## Abstract

**Background:**

Despite extensive efforts, issues like obesity and poor physical capacity remain challenges for a healthy work life in several occupations. The Goldilocks work principle offers a new approach, encouraging design of productive work to promote physical capacity and health. This paper presents the protocol for the Goldilocks-childcare study, a randomised controlled intervention trial aiming to evaluate the effectiveness of implementing the Goldilocks work principle in childcare. The primary aim of the intervention is to increase time in moderate to vigorous physical activity (MVPA) by having the childcare workers act as active role models for children in daily playful physical activities, and thereby improve cardiorespiratory fitness and health of the workers.

**Methods:**

The study is a cluster-randomised trial with a usual-practice wait-list control group. The 10-week intervention consists of two phases. In the first, the childcare workers will participate in two participatory workshops aiming to a) develop playful physical activities (‘Goldilocks-games’) for children in which childcare workers participate as active role models at MVPA intensity, and b) develop action plans for implementation of the Goldilocks-games in daily work routines. In the second phase, childcare institutions will implement the Goldilocks-games. The primary outcome is working time spent in MVPA, and secondary outcomes are cardiorespiratory fitness, sleeping heart rate, perceived need for recovery, and productivity. Primary outcome and process evaluation will be based on direct measurements of physical activity and heart rate, determination of cardiorespiratory fitness, and questionnaires.

**Discussion:**

If proven effective, the Goldilocks work principle has a large potential for promoting sustainable health and working lives of childcare workers.

**Trial registration:**

ISRCTN, ISRCTN15644757, Registered 25th December 2019

## Background

Despite extensive efforts to promote occupational health, several occupations still face considerable challenges in achieving a long, healthy, and sustainable work life for those employed. Examples of these challenges are the increased occurrence of obesity in the working population [1], and a considerable proportion of workers not having the physical capacity required for performing their main work tasks [2]. Both issues are associated with social inequality in health [3], and particularly pronounced in an ageing working population [4].

The dominant approach to prevent work-related disorders has consisted of reducing the physical activity demands at work [5]. Accordingly, the intensity of occupational physical activity has been minimised in many occupations, most often by increasing the amount of sedentary time [6]. To compensate for insufficient physical activity at work, numerous workplace health promotion initiatives have then attempted to improve employees’ physical capacity and health by offering physical exercise at the workplace [7, 8]. However, these initiatives have not been successful in reaching the employees most in need [9–11]. Also, workplace physical exercise programmes are often not appealing to employers, since they require time away from productive work, and thus being a costly initiative. Therefore, both minimising physical activity and introducing exercising during working hours are inadequate to solve the abovementioned challenges in occupational health [12].

As an alternative, the Goldilocks work principle has been proposed [12, 13], aiming to design productive work in a way that promotes physical capacity and health without compromising productivity [12, 13]. Building on work physiology fundamentals [14], the Goldilocks work principle seeks to achieve a ‘just right’ balance between physical activity demands and recovery at work, so that a training effect can be obtained from the work per se, leading to better health [12]. However, the effectiveness of the Goldilocks work principle remains to be evaluated in randomised controlled trials.

Childcare workers generally report a high prevalence of poor general health, physical work exertion, musculoskeletal pain, and sickness absence [15–17]. Moreover, childcare workers have been shown to spend only a small amount of work time in moderate to vigorous physical activity (MVPA) [18]. In a pilot study conducted among childcare workers, we found workers were sitting extensively and had minimal work time in MVPA. Because MVPA is well documented to improve cardiorespiratory fitness and health [19], we believe that an increase in MVPA in the daily routines of childcare workers could have a great potential to lead to better health and more sustainable work.

An important general aim in childcare is to encourage children to be more physically active [20, 21]. Therefore, by acting as active role models in daily playful physical activities (termed ‘Goldilocks-games’) together with the children, the childcare workers may be able to achieve sufficient daily work time in MVPA to improve their own cardiorespiratory fitness and health. However, this has not been evaluated in a randomised controlled trial among childcare workers.

The aim of this protocol paper is to describe the design, implementation, and evaluation of the participatory randomised controlled trial ‘Goldilocks-childcare’, which seeks to increase the childcare workers’ productive work time spent in MVPA, and thus their cardiorespiratory fitness and health.

## Methods/ design

### Data protection, ethical approval, and trial registration

The National Research Centre for the Working Environment has an institutional agreement with the Danish Data Protection Agency about procedures to treat confidential data (journal number 2015-41-4232), e.g. by securing data at a protected drive with limited access, and by anonymizing all individual data.

The Danish National Committee on Biomedical Research Ethics (The local ethical committee of Frederiksberg and Copenhagen) has evaluated a description of the study and concluded that, according to Danish law as defined in Committee Act § 2 and § 1, the intervention described should not be further reported to the local ethics committee (Ref number: H-18041423).

The study is registered in the International Standard Registered Clinical/soCial sTudy Number (ISRCTN) registry (ISRCTN15644757). The protocol conforms to the Standard Protocol Items: Recommendations for Interventional Trials (SPIRIT) 2013 statement [22] and the Template for Intervention Description and Replication (TIDieR) checklist [23]. The reporting of the study will follow the Consolidated Standards of Reporting Trials (CONSORT) 2010 statement [24].

### Study design

Figure 1 provides an overview of the study design. The study will use a cluster-randomised design with a usual-practice wait-list control group. As the study is an organisational intervention in a work place setting, individual randomisation is neither possible nor appropriate [25]. Thus, each participating institution will form a cluster. A wait-list design (offering the intervention to the intervention and, eventually, even to the control groups) was chosen in an attempt to minimise any potential lack of commitment from an institution acting as control [26]. Thus, we will randomly assign the participating childcare institutions to, i) the intervention group immediately receiving the intervention after the baseline measurements or, ii) the control group continuing usual practice for 10 weeks after the baseline measurements and then performing the intervention. Each intervention period will last 10 weeks. After the 10 weeks intervention for the intervention group, they will be encouraged to continue with Goldilocks-games without further support from the research team.

**Fig. 1 Fig1:**
[figure not shown]
Study design. W1 = A two-and-a-half-hours workshop (Workshop 1) explaining the overall concept of the Goldilocks work principle. CV 1 = Consultant visit at the childcare institutions performed by the work environment consultants. W2 = A one-and-a-half-hour follow-up workshop (Workshop 2). CV2 = a consultation phone call with a member of the Trio 2 weeks after Workshop 2

Recruitment of childcare institutions opened in March 2019 and will continue until the sufficient number of childcare institutions required for the trial are enrolled. Recruitment of participants at the participating childcare institutions will open in January 2020. The intervention will start in January 2020 with the participants enrolled in the childcare institutions recruited first. The last childcare institutions enrolled in the trial will start the intervention by September 2020.

### Study population

The childcare institutions are recruited from the greater Copenhagen area in collaboration with employer organisations, unions, and local government municipalities. In order to be eligible for participation, the childcare institution should employ a minimum of nine childcare workers.

As the intervention is organisational, all employees within the participating childcare institutions will take part in the intervention activities, and all childcare workers will be eligible for participation in the trial evaluation. Since this participation is voluntary, the childcare workers will, prior to entering the trial, be provided with information about the trial, asked if they agree to participate, and if so, asked to sign an informed consent form.

### Randomisation and blinding

Cluster-randomisation will be used with each childcare institution constituting a cluster, in order to avoid contamination within an institution between participating and non-participating workers. Participating childcare institutions will be randomised to either intervention or usual practice (i.e. wait-list control) arms of the trial. This randomisation will be conducted upon enrolment of each participating childcare institution into the study. The randomisation sequence has been developed using the statistical software R [27].

Because of the time needed for the childcare institutions to plan their participation in the trial, we need to inform them about their allocation to intervention or control group before the baseline data collection. Moreover, due to the nature of the trial, it will not be possible to blind neither the researchers nor the participating employees as regards whether a particular institution is subject to the intervention or not. However, allocation concealment will be maintained throughout the study, and all researchers conducting the randomisation, statistical analysis, and evaluation will be blinded.

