**Fig. 4 Fig4:**
[figure not shown]
Standard Protocol Items: Recommendation for Interventional Trials (SPIRIT) schedule of enrolment, interventions, and assessments. W = Workshop; CV = Consultant visit; FU = Follow up; MVPA = Moderate to Vigorous Physical Activity. *Randomisation carried out at childcare institution level before baseline measurements. **The study uses a wait-list design; control group institutions will receive the intervention after the intervention group

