The main limitation of the study is the lack of allocation concealment, which introduces the risk of selection bias. This is, however, inevitable since the study design requires the participating childcare institutions to make organisational changes that build on a participatory approach. Thus, the participating childcare institutions need to be informed of their allocation in advance, in order to facilitate their introduction of organisational changes as well as allowing them adequate time for preparing and initiating any required logistics, e.g. staffing issues or equipment. Also, blinding the participants is, for natural reasons, not possible. This is a common issue in participatory interventions, and it may introduce a risk of unintended effects, e.g. a possible placebo change in the selected outcome(s), or a Hawthorne effect [62]. However, we will try to minimise both of these limitations. All participants will, eventually, receive the intervention, participants are only informed about when the intervention will be implemented at their institution, and not whether they are allocated to an intervention or a control group in the actual intervention project. Thus, the lack of blinding is expected to have no or minimal influence on the results of the study.

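### The protocol says both that allocation concealment is maintained and that it is lacking, and its sequence of events probably lets workers consent to the evaluation with their institution's arm known.

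*Protocol article*

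**What the plan says.** Under Randomisation and blinding, the Protocol article states that "allocation concealment will be maintained throughout the study, and all researchers conducting the randomisation, statistical analysis, and evaluation will be blinded". The sentence just before it says that neither researchers nor employees can be blinded. Under Strengths and limitations of the study, the article says: "The main limitation of the study is the lack of allocation concealment, which introduces the risk of selection bias".

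On timing, the same randomisation section says "This randomisation will be conducted upon enrolment of each participating childcare institution into the study" and, because institutions need time to plan, "we need to inform them about their allocation to intervention or control group before the baseline data collection". The footnote to Fig. 4 confirms the order: "Randomisation carried out at childcare institution level before baseline measurements". The Study design section adds "Recruitment of childcare institutions opened in March 2019" and "Recruitment of participants at the participating childcare institutions will open in January 2020". Under Study population, all employees take part in the intervention activities, while entry to the trial evaluation is voluntary and needs individual signed consent.

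The limitations section calls the concealment problem inevitable and says that the investigators will try to reduce it and the lack of blinding. Part of its argument is that "participants are only informed about when the intervention will be implemented at their institution, and not whether they are allocated" to one group or the other. It then concludes that the lack of blinding should have little or no influence on the results.

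**The concern.** There are three linked problems.

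1. **Concealment.** The protocol claims a safeguard in one section and denies it in another. A reader cannot tell which safeguard exists, and a later report could cite either sentence.
2. **Blinding.** Two consecutive sentences say that researchers cannot be blinded and that the researchers doing randomisation, analysis and evaluation are blinded. The text does not say whether these are different people.
3. **Recruitment after randomisation.** In a cluster trial, randomising institutions protects the comparison of individuals only if the arm does not influence who joins. If workers decide on consent after the arm is known, consenters in the two arms may differ in motivation, and so in how much they change over 10 weeks.

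The self-reported secondary outcomes, need for recovery and productivity, are the most exposed to the lack of blinding, because the sensors protect only what they measure.

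**Working it through.** No stated figure underlies this point, so the check compares the text and rebuilds the order of events.

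**Concealment.** The randomisation section says that concealment is maintained throughout. The limitations section says that it is lacking and is the main limitation. Neither is an amendment log. The two could be reconciled if the first meant that the sequence is hidden until an institution is committed, and the second that the arm is not hidden from those who join later. The article does not draw that distinction.

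**Order of events.**

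| Step | Timing given | Where |
|---|---|---|
| Institution enrols | from March 2019, planned to September 2020 | Study design; Trial status |
| Institution is randomised | on enrolment | Randomisation and blinding |
| Institution learns its arm | before baseline, no date | Randomisation and blinding |
| Workers are recruited and consent | from January 2020 | Study design; Study population |
| Baseline is measured | after randomisation | Fig. 4 footnote |
| First interventions start | January 2020 | Study design; Trial status |

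- From March 2019 to January 2020 is 10 months. For any institution enrolled in that window, randomisation necessarily precedes worker consent.
- The document does not date disclosure against consent. However, worker recruitment and the first interventions both open in January 2020, and consent and baseline must come before the intervention. Institutions that need planning time before baseline would then have to know their arm at about the time their workers could consent, or earlier. Disclosure before consent is therefore probable but not stated.

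**Does telling workers only the start time hide the arm?** There are two arms. One starts straight after baseline and the other 10 weeks later. Each start time corresponds to exactly one arm, so knowing the start time is knowing the arm. The randomisation section itself accepts that employees cannot be blinded.

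**Is consent with the arm known inevitable?** The stated reasons are planning, staffing and logistics. They require the institution to know its arm some time before baseline. They do not require workers to consent after that. The order consent, disclosure, planning, baseline satisfies the stated need.

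**What kind of bias would remain?** The Primary and secondary outcomes section compares changes from baseline to 10 weeks. Suppose a share *p* of intervention-arm participants would not have joined as controls. Let them differ from the other participants by *d* in level and by *g* in change, apart from any effect of the intervention on the others. Then:

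- gap between arms at baseline = *p* × *d*
- gap between arms at 10 weeks = *p* × (*d* + *g*)
- difference in changes = *p* × (*d* + *g*) − *p* × *d* = *p* × *g*

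The stable level difference *d* drops out of this simple contrast, and largely so in a multilevel model built on it. The term *g* stays: keener volunteers may respond more, or an unusual baseline may regress to the mean. The document gives neither *p* nor *g*, so no size can be computed.

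**The case against.** The strongest reply has five parts.

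- **The protocol is candid about selection.** A reader might infer that it claims to avoid recruitment bias. It does not. The limitations section concedes the risk, and only the concealment sentence in the randomisation section implies protection. The claim of little or no influence concerns lack of blinding, not recruitment. This stands.
- **Disclosure before consent is not stated.** A reader might take it as fact that workers join with the arm known. The text fixes disclosure before baseline only, so this is a strong inference. This also stands.
- **The incentive is weak.** Consent covers only the evaluation, and all employees take part in the activities. A keen worker gets the games without consenting. This weakens the mechanism but does not remove it: willingness to be measured and tested may still depend on whether the institution is about to start.
- **The analysis protects against level differences.** The outcome is change from baseline, and the Statistical analysis section adjusts for baseline differences in factors such as age and BMI. A reader might want to express the bias in SD units by assuming a share of extra volunteers and a gap in level. The documents do not support such a figure, because that gap would largely cancel. Differential change is not reliably removed by these covariates.
- **The two blinding sentences may refer to different people,** such as field staff and analysts. That is possible, but the text does not say so. This is unclear wording, and a weaker point than the contradiction on concealment.

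**Conclusion.** The contradiction on concealment is plain on the face of the text, and the unqualified claim that it is maintained should not stand. The statement on who is blinded is unclear. The order of randomisation, disclosure and worker recruitment leaves the trial open to post-randomisation recruitment bias. The protocol admits this risk, but its stated reason does not make it inevitable. The argument that workers learn only the start time does not support a minimal influence of unblinding, least of all for need for recovery and productivity.

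The recruitment conclusion rests on one assumption, that institutions, and through the start time their workers, know the arm by the time of consent. The dates make this probable. The size of the bias is unknown, and what matters is differential change. I would therefore rank this as a correction of the text plus a cheap improvement to the design, not as a fault that by itself invalidates the trial.

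**What to change.** 1. In Randomisation and blinding, remove the concealment claim, or limit it to hiding the sequence until an institution is irrevocably enrolled if that is what is done. Align it with the limitations section.
2. State exactly who is blinded and to what, and how this fits with the sentence that researchers cannot be.
3. State when workers consent relative to disclosure of the arm. For every institution not yet informed, close the list of consenting workers before releasing the allocation.
4. Report the numbers of eligible and consenting workers by arm for all institutions, including those already informed.
5. Withdraw the argument that telling workers only the start time makes the influence of unblinding minimal, and say that the self-reported secondary outcomes are the most exposed.

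Items 1, 2 and 5 are wording, and item 4 is a count. Item 3 needs an earlier consent contact at each remaining institution and accepts some staff turnover between consent and baseline. The document gives no lead time between disclosure and baseline, so the length of that gap cannot be stated. With enrolment planned to run to September 2020, the change can still help institutions that have not been told their arm. It cannot repair those already informed, for which item 4 is the available check.

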### Intervention

The overall study idea was developed in collaboration between the researchers and work environment consultants (Physiotherapists and Occupational therapists) from the Work Environment Consultancy of Copenhagen Municipality (WECoCM), based on the Goldilocks work principle [12].

To ensure that the intervention is relevant for, tailored to, and closely integrated with pedagogical teaching aims as well as feasible for the childcare institutions, the intervention will apply a participatory approach. The Goldilocks work principle for the intervention content and implementation is explained and modified on the basis of a dialog with stakeholders related to childcare (e.g. employer organisations and unions, practitioners in childcare, work environment consultants), of observations of childcare work, and of a dialog with managers and employees in childcare institutions.

Further, the manager, a union representative, and an occupational health and safety representative (collectively referred to as the Trio) from each of the participating childcare institutions will attend a workshop. The workshop will outline the Goldilocks work principle for all institutions and aim to facilitate planning and management support to the implementation and evaluation of the intervention. The Trio will then be involved in planning and tailoring the intervention process to their own childcare institution. Thus, the Trio is responsible for outlining the pedagogical focus, rostering and practical planning at their institutions. Involving the Trio at an early stage will enhance the likelihood of organisational buy-in and the possibility for introducing organisational changes.

To facilitate development and implementation of the Goldilocks-games, we will conduct a proof of concept study in a few childcare institutions. The proof of concept study will focus on development and evaluation of feasible Goldilocks-games that can increase the occurrence of MVPA among the childcare workers. Experiences from this proof of concept study will be applied in the first workshop at each institution participating in the randomised controlled trial.

A programme logic model for the Goldilocks work principle was developed (Fig. 2). The programme logic model provides a schematic overview of the steps from introducing the Goldilocks work intervention to the effects on cardiorespiratory fitness and health of the childcare workers. In addition, the programme model assists in guiding the effect and process evaluation.

